### Specific hygienic measures

Due to the first in man application of a replication competent parvovirus and the lack of data about the toxicity and excretion of the IMP in humans after intracerebral or intravenous injection specific procedures have to be applied. Despite low hygienic risks associated with the current trial a number of hygienic measures have to be adhered to (Table 2).

**Table 2 T2:** Specific hygenic measures

• Information of staff involved in the medical care/nursing of trial subjects (e.g. physicians, nurses, cleaning staff, physiotherapist),
• Proposal of serological testing of medical staff for H-1PV prior to the beginning and at the end of the trial (in order to document potential seroconversion),
• Consideration of a subject as potentially viremic until:
○ A seroconversion as proven by HIT or ELISA, ○ In the absence of a seroconversion until proven lack of virus shedding in urine, saliva, and feces,
• While a subject is considered as potentially viremic:
○ Isolate her/him in a single room with its own toilet, ○ Use disposable gloves, protection gown and mask for handling of study medication and materials contaminated with ParvOryx, e.g. infusion materials, ○ Information of medical staff to use gloves, protection gown and mask when in physical contact with the patient, ○ Information of medical staff and visitors to use mask only when strictly omitting body contact with the subject during his/her isolation phase. Alternatively, the subject can wear a mask when in the same room with medical staff and visitors, ○ Information of hygiene staff to carry out a terminal disinfection after discharge of a subject from isolation, ○ In case of surface contamination the disinfection must be performed with Perform^®^, 3%

ParvOryx01 is the first in man application of a GMP grade oncolytic parvovirus. The hygienic precautions listed above must be applied including isolation of patients in a single room as long as they are considered viremic. Virus shedding and seroconversion are tested daily to reduce duration of isolation to a minimum

### Benefit/risk assessment

Currently, recurrent glioblastoma is a tumor entity for which no established standard of care exists. The prognosis of this disease is dismal, the progression free survival at 6 months (6 M-PFS) ranges between 15% to 21% and the median survival of patients is in the range of 25 weeks [19]. Re-operation is one possible treatment option with proven clinical benefit. It can be estimated that one third of patients with recurrent GBM are candidates for a second debulking surgical procedure.

Non-surgical treatment options include the application of re-irradiation for a subset of approximately 20% of patients and the use of chemotherapy. None of these treatments has been shown to have a major impact on PFS or survival.

The use of replication competent Parvovirus H-1 in the current trial setting therefore addresses a patient population without a standard of care and with only limited treatment options. According to the study protocol even without oncolytic efficacy of H-1PV patients would benefit from participating in the trial due to re-operation after initial virus treatment.

There is only limited information about the effects of Parvovirus H-1 infections of humans, but according to the assessment of the pathogenicity of the virus in humans by the Robert Koch Institut it is classified as non-pathogenic in man. This is supported by the limited available information from human patients. According to data from Parvovirus H-1 application in terminally ill tumor patients in 1965 and in 1993 the injection(s) did not cause severe side effects. The virus that was used in these patients (n = 2 in 1965 and n = 12 in 1993) was not produced according to today's GMP standard and the amount of virus that was injected was in the range from approx. 2 × 10 exp8 to approx. 3 × 10 exp10 [20,21]. Recently, it could also be demonstrated that even laboratory staff who had worked with Parvovirus H-1 for several years was tested negative for Parvovirus H-1 specific antibodies, ruling out active infection and pointing to a very low level of contagiousness of H-1PV in humans ([name], German Cancer Research Center (DKFZ), personal communication).

The virus batch that was produced under GMP conditions for use in this clinical trial was tested extensively in animals to obtain toxicology data. Toxicology testing included intravenous and intracerebral administrations. In the repeat dose toxicology study multiple intravenous injections over a 28 day period at 3 different dose levels (low, medium, high) were employed. The only safety issue diagnosed by histology but not by clinical or laboratory abnormalities was a minimal bile duct proliferation observed in some animals of the highest and in one animal of the middle dose group after repeated applications. No other relevant pathological findings that could be attributed to H-1PV were observed, confirming that even multiple injections of high virus titers are not associated with severe side effect. Thus, injection of H-1PV according to this trial protocol can be assumed to possesses only a low risk of side effects in patients with a life threatening disease.

Due to the lack of relevant pathogenicity of H-1PV in humans, viral shedding by injected patients with subsequent symptomatic infections of unrelated subjects is extremely unlikely. In addition, patients will be isolated after virus treatment until no virus shedding can be demonstrated by real-time PCR or virus specific antibodies are present. This in combination with specific hygiene precautions further minimizes the risk for the environment and for hospital staff or other subjects.

### Statistical analysis

#### Analysis variables

The primary criterion for dose modification is the relative frequency of a dose-limiting event (DLE) at a given dose level. Toxicity of a dose is defined as the probability of this dose being associated with a DLE in a patient as indicated in the trial protocol. A dose is defined as tolerable if the probability of toxicity is lower than 33 per cent. The maximum tolerated dose is defined as the dose level with the highest posterior probability of having a toxicity not higher than 33 per cent.

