### Sample size

The current trial represents the first in man study with the IMP (ParvOryx). 18 subjects will be allocated to 2 study groups with 9 subjects per group. Per group, 3 dose levels will be investigated. The mean number of 3 subjects per dose level appears to be sufficient to give first indications about safety, tolerability and proof of concept of ParvOryx.

There will be no a-priori defined quantitative ratio between females and males. However, no gender differences in the safety, tolerability as well as efficacy are expected on the basis of preclinical findings.

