#### Statistical methods

The posterior probability for toxicity will be calculated in a logistic model, where the toxicities are parametrized as follows: *p_ij_*: toxicity for group i, level j, $\text{log}\left(p_{i1}/\left(1-p_{i1}\right)\right)=a_{i}-\beta_{i;}\text{log}\left(p_{i2}/\left(1-p_{i2}\right)\right)=a_{i}\text{log}\left(p_{i3}/\left(1-p_{i3}\right)\right)=a_{i}+\beta_{i};$ with the following prior distribution for the intercept and slope parameters:

$$\left(\alpha_{1},\beta_{1},\alpha_{2},\beta_{2}\right)\sim N\left(\left(\begin{array}{c} 0\\ 0\\ 0\\ 0 \end{array}\right),\left(\begin{array}{cccc} 4 & -.2 & 1.6 & 0\\ -.2 & 4 & 0 & 1.6\\ 1.6 & 0 & 4 & -.2\\ 0 & 1.6 & -.2 & 4 \end{array}\right)\right)$$

Whenever a subject enters the study, the dose level will be elicited by calculating the posterior probability for each dose level to be tolerable. The highest dose level that is tolerable will be allocated.

The following measurements will be subject to descriptive statistical methods: vital signs, serum levels and hematology data, H-1 PV specific antibodies, virus shedding. Progression Free Survival and Overall Survival will be listed per group and subject, showing observation time and event status.

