#### Dose escalation scheme

As long as no DLE is observed, a classic three-at-one design will be followed [22]. After the first DLE is observed one more patient will be recruited at the same dose before the dose will be determined as the maximum tolerated dose following the model outlined above. The highest dose with a median probability of tolerability being at least 33 per cent will be applied as the current MTD to the subsequent patient, following the Continual Reassessment Method [23]. If the MTD is ever to be calculated as being "dose 0", the trial ends prematurely at any time with the result that no safe dose could be established (Figure 2). Nine consecutive patients will be allocated to Group 1 before nine more patients will be allocated to Group 2. As the metaparameters α and β are assumed to be correlated between groups, results from group 1 affect the escalation scheme in group 2.

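### The MTD is defined as the dose level most surely below 33% toxicity, which conflicts with the article's own highest-tolerable-dose rules and gives level 2, not level 3, when no DLE occurs

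*Protocol article*

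**What the plan says.** The protocol article gives three rules that bear on the MTD.

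- **Analysis variables** sets the threshold: "A dose is defined as tolerable if the probability of toxicity is lower than 33 per cent". It then gives the only formal definition of the MTD, namely "the dose level with the highest posterior probability of having a toxicity not higher than 33 per cent".
- **Statistical methods** governs which level a new subject receives: "The highest dose level that is tolerable will be allocated".
- **Dose escalation scheme** takes as the current MTD for the next patient the highest dose whose median probability of tolerability reaches 33 per cent. If the result is 'dose 0', "the trial ends prematurely at any time with the result that no safe dose could be established".

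The MTD is listed under Primary objectives. The Discussion adds that tolerability in group 1 will be judged again at the end, using group 2 results. The reported MTD is thus a separate step from the running MTD used for allocation.

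**The concern.** The formal definition chooses the level that maximises the probability of being under the threshold. The other two rules choose the highest level that passes it. These are different questions. When toxicity rises with dose, the probability of being under 33% cannot rise with dose, so maximising it favours a level below the highest one that qualifies.

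The gap is widest when few or no DLEs occur. The Benefit/risk assessment expects exactly that outcome, since it assumes only a low risk of side effects. The trial could then report, as its primary result, a level below the highest one that its own model finds tolerable.

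Read alone, the defining sentence also always returns one of the three levels and has no 'dose 0' outcome. That outcome appears only in Dose escalation scheme.

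**Working it through.** The article prints no numerical MTD result, and its escalation figure is not shown, so there is no stated figure to reproduce. The check applies the printed model.

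**Inputs**
- Model (Statistical methods: "The posterior probability for toxicity will be calculated in a logistic model"): logit p₁ = α − β, logit p₂ = α, logit p₃ = α + β within each group.
- Prior (Statistical methods): normal, all means 0, all variances 4, within-group cov(α, β) = −0.2, between-group covariance 1.6 for the α pair and for the β pair. No positivity constraint on β is printed.
- Threshold (Analysis variables): 0.33, that is logit = ln(0.33/0.67) = −0.708.
- Levels and patients: "Per group, 3 dose levels will be investigated" (Sample size) and "As long as no DLE is observed, a classic three-at-one design will be followed" (Dose escalation scheme). Without a DLE, 3 + 3 + 3 = 9 patients are treated per group.

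**Formulas**
- Posterior ∝ prior(α, β) × ∏ⱼ pⱼ^xⱼ (1 − pⱼ)^(nⱼ − xⱼ), integrated on a grid.
- Tⱼ = P(pⱼ ≤ 0.33 | data).
- Defined MTD = the level with the largest Tⱼ. Highest-dose rule = the largest j that passes the cut-off.

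**Group 1 results**

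| DLEs at levels 1, 2, 3 | β | T₁ | T₂ | T₃ | Defined MTD |
|---|---|---|---|---|---|
| 0/3, 0/3, 0/3 | as printed | 0.941 | 0.993 | 0.935 | level 2 |
| 0/3, 0/3, 1/3 | as printed | 0.963 | 0.953 | 0.584 | level 1 |
| 0/3, 1/3, 0/3 | as printed | 0.835 | 0.938 | 0.828 | level 2 |
| 1/3, 0/3, 0/3 | as printed | 0.594 | 0.950 | 0.959 | level 3 |
| 0/3, 0/3, 0/3 | restricted to β > 0 | 0.998 | 0.993 | 0.877 | level 1 |

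With no DLE, level 3 has T₃ = 0.935 and a posterior median toxicity of 0.053. It passes the cut-off however the 33 per cent is read, so the highest-dose rules return level 3. A threshold of 1/3 changes little (0.942, 0.993, 0.936). In the joint model with no DLE in either group the values are about 0.959, 0.997 and 0.956 in each group, so the definition gives level 2 in both.

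**Why level 2.** Level 2 depends on α alone, with prior variance 4. Level 1 has var(α − β) = 4 + 4 + 2(0.2) = 8.4, and level 3 has var(α + β) = 4 + 4 − 2(0.2) = 7.6. With no events, the level with the least uncertainty wins.

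**Why level 1 if β > 0.** Then p₁ < p₂ < p₃ throughout. Whenever p₂ ≤ 0.33, p₁ ≤ 0.33 as well, so T₁ ≥ T₂ ≥ T₃ for any data.

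**How often.** All group 1 paths were enumerated under assumed true rates of 5/10/20%, where every level is below 33%. The wording of the cut-off in Dose escalation scheme allows two readings.

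| Cut-off read as | Defined MTD is level 1 / 2 / 3 | Highest-dose rule gives level 3 |
|---|---|---|
| P(tolerable) ≥ 50%, i.e. median toxicity ≤ 33% | 60% / 34% / 6% | 50% |
| P(tolerable) ≥ 33% | 47% / 46% / 8% | 78% |

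These figures apply the definition to every path, including those already ended at 'dose 0'. Under the first reading, all of the 6% are such ended trials. Under the second, most of the 8% ran to nine patients.

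**The case against.** The best defence is that the defining sentence is a badly compressed version of the highest-dose rule. Statistical methods and Dose escalation scheme agree in direction, fit the ordinary meaning of a maximum tolerated dose, and govern allocation and stopping. The data safety monitoring board must also consent to each new level. No patient's dose depends on the sentence. This stands: the exposure is limited to the reported MTD. It does not remove the conflict, because Dose escalation scheme sets only the running MTD for the next patient. The formal definition is therefore the one that applies to the reported MTD. The article condenses a fuller protocol, but it does state a definition, and that definition contradicts its later text.

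Three stronger readings are tempting and are not supported.

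- A reader might infer that the plan cannot declare that no level is safe. Taken as a whole it can: Dose escalation scheme ends the trial with that result.
- A reader might infer that a very toxic product would be labelled with level 3. Under assumed rates of 70/80/90% the criterion does point there often. However, all of those cases (first reading of the cut-off) or nearly all (second reading) are trials already ended with no safe dose.
- A reader might infer that the definition always selects a low level. Under the printed prior, which allows negative slopes, it does not: 1/3, 0/3, 0/3 gives level 3.

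The percentages also depend on how the cut-off is read, so they are given as a range.

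**Conclusion.** The definition is wrong as written and contradicts two other sections. With the printed model and no DLE it reports level 2, although level 3 has a posterior probability of about 0.94 of being under the threshold. That result holds for a threshold of 0.33 or 1/3 and for group 1 alone or both groups together; restricting the slope to be positive moves the answer to level 1. No variant tried with zero DLEs gives level 3.

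Under the assumed 5/10/20% scenario, the definition names level 3 in about 6 to 8% of group 1 trials, against 50 to 78% for the highest-dose rule. These frequencies rest on the assumed rates and on the two readings of the cut-off. The zero-DLE result and the conflict between sections do not.

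The error affects how a primary objective is reported, in the outcome that the sponsor expects. It does not affect allocation, and it does not leave the plan without a no-safe-dose result.

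**What to change.** Delete the highest-posterior-probability wording in Analysis variables. Reconcile that section with Statistical methods and Dose escalation scheme so that one statistical definition of the reported MTD remains. It should follow the article's own principle of the highest tolerable dose and include its 'dose 0' outcome. The sponsor should state which reading of the 33 per cent cut-off applies (posterior median toxicity against 33%, or probability of tolerability against 33%) and say whether the final judgement using both groups follows the same definition.

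The cost is a sentence or two of text. No dose, stopping rule, patient number or data collection needs to change.

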#### Statistical methods

The posterior probability for toxicity will be calculated in a logistic model, where the toxicities are parametrized as follows: *p_ij_*: toxicity for group i, level j, $\text{log}\left(p_{i1}/\left(1-p_{i1}\right)\right)=a_{i}-\beta_{i;}\text{log}\left(p_{i2}/\left(1-p_{i2}\right)\right)=a_{i}\text{log}\left(p_{i3}/\left(1-p_{i3}\right)\right)=a_{i}+\beta_{i};$ with the following prior distribution for the intercept and slope parameters:

$$\left(\alpha_{1},\beta_{1},\alpha_{2},\beta_{2}\right)\sim N\left(\left(\begin{array}{c} 0\\ 0\\ 0\\ 0 \end{array}\right),\left(\begin{array}{cccc} 4 & -.2 & 1.6 & 0\\ -.2 & 4 & 0 & 1.6\\ 1.6 & 0 & 4 & -.2\\ 0 & 1.6 & -.2 & 4 \end{array}\right)\right)$$

Whenever a subject enters the study, the dose level will be elicited by calculating the posterior probability for each dose level to be tolerable. The highest dose level that is tolerable will be allocated.

The following measurements will be subject to descriptive statistical methods: vital signs, serum levels and hematology data, H-1 PV specific antibodies, virus shedding. Progression Free Survival and Overall Survival will be listed per group and subject, showing observation time and event status.

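### The slope prior allows toxicity to fall with dose: after a clean group 1, two DLEs in two patients at intravenous level 1 leave level 3 as the model's choice

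*Protocol article*

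**What the plan says.** All references are to the protocol article.

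- **Statistical methods.** "The posterior probability for toxicity will be calculated in a logistic model, where the toxicities are parametrized as follows": level 1 is α−β, level 2 is α and level 3 is α+β on the logit scale, separately for each group. The model comes "with the following prior distribution for the intercept and slope parameters": jointly normal, with all means 0, all variances 4, within-group covariance of intercept and slope −0.2, and between-group covariance 1.6 for intercepts and for slopes. No truncation or sign restriction is given.
- **The tolerability limit** (Analysis variables): "A dose is defined as tolerable if the probability of toxicity is lower than 33 per cent".
- **The allocation rule appears in three wordings.** One stands in Analysis variables: "The maximum tolerated dose is defined as the dose level with the highest posterior probability of having a toxicity not higher than 33 per cent". A second wording, in Statistical methods, is: "The highest dose level that is tolerable will be allocated". Under Dose escalation scheme the rule reads: "The highest dose with a median probability of tolerability being at least 33 per cent will be applied as the current MTD to the subsequent", that is, to whoever is treated next.
- **When the model decides** (Dose escalation scheme): "As long as no DLE is observed, a classic three-at-one design will be followed". After the first DLE one more patient is treated at the same dose, and the model then sets the next dose. A calculated dose 0 ends the trial.
- **Borrowing** (Dose escalation scheme): "As the metaparameters α and β are assumed to be correlated between groups, results from group 1 affect the escalation scheme in group 2".

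**The concern.** Allocating the highest tolerable level, as in the Continual Reassessment Method that the article invokes, makes sense only if toxicity does not fall as dose rises. A DLE at a low level should then count at least as heavily against every higher level. A slope prior centred at 0 without a sign constraint drops that assumption. The model can account for toxicity at level 1 by a negative slope and still regard level 3 as tolerable, although the total dose there is 1000 times higher (1 × 10^6 against 1 × 10^9 pfu in Table 1).

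At stake are the next-patient allocation, the dose-0 stopping rule, and the MTD, which is listed under the primary objectives of this first-in-man trial.

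**Working it through.** The article prints no posterior figure to reproduce, so everything below is computed from its printed model and prior.

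**1. Prior, by hand.**
- P(β<0) = 0.50, because β is normal with mean 0.
- Within a group: Cov(α−β, α+β) = Var(α) + Cov(α,β) − Cov(β,α) − Var(β) = 4 − 0.2 + 0.2 − 4 = 0.
- Across groups: Cov(α1−β1, α2+β2) = 1.6 + 0 − 0 − 1.6 = 0.

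Under joint normality, level 1 in either group is a priori independent of level 3 in either group.

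**2. Posterior after a clean group 1 (0/3, 0/3, 0/3).** Posterior ∝ prior × binomial likelihood, from 4,000,000 weighted prior draws (effective sample size about 247,000 in the 2/2 row). A deterministic grid with Gauss–Hermite integration agrees within about 0.01. Values are for group 2, levels 1/2/3.

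| DLEs at IV level 1 | Median toxicity | P(toxicity ≤33%) |
|---|---|---|
| none treated | 0.23/0.22/0.22 | 0.57/0.61/0.59 |
| 1/2 | 0.42/0.31/0.22 | 0.38/0.53/0.59 |
| 2/2 | 0.86/0.58/0.21 | 0.04/0.25/0.59 |
| 3/3 | 0.90/0.62/0.21 | 0.01/0.21/0.59 |
| 1/3 | 0.29/0.25/0.22 | 0.57/0.61/0.59 |
| 2/3 | 0.61/0.40/0.22 | 0.15/0.42/0.59 |
| 1/4 | 0.22/0.21/0.22 | 0.70/0.67/0.59 |
| 2/4 | 0.46/0.33/0.22 | 0.29/0.51/0.59 |

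The level 3 figures barely move in any row. After 2/2, P(β2<0) is 0.85. The 3/3 row is a sensitivity check: if the model is followed, it already decides at 2/2.

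**3. Rules applied to 2/2.** The largest P(toxicity ≤33%) is 0.59, at level 3. The highest level with median toxicity below 0.33 is level 3 (0.21). The highest level with P(tolerable) of at least 0.33 is level 3 (0.59). Reading the third wording literally, as median of 1 − toxicity of at least 0.33, also gives level 3 (1 − 0.21 = 0.79). The 1/2 and 3/3 rows give level 3 too.

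**4. Chance of reaching level 3 by this route.** Let r be the true DLE rate at IV level 1, after a clean group 1.
- *Highest-level wordings.* Level 3 qualifies in every row, so any DLE among the first three IV patients suffices: 1 − (1−r)³ = 1 − 0.9³ = 27% for r = 10%, and 1 − 0.67³ = 70% for r = 33%.
- *Highest-posterior-probability wording.* 1/3 selects level 2 and 1/4 selects level 1. Level 3 needs a DLE in patient 1 (then 1/2 or 2/2), or a first DLE in patient 2 or 3 followed by a second in the added patient (2/3 or 2/4): r + (1−r)r² + (1−r)²r².
  - r = 10%: 0.100 + 0.009 + 0.008 = 12%.
  - r = 33%: 0.330 + 0.073 + 0.049 = 45%.

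**5. Group 1 on its own.** With 2/2 DLEs at level 1, the medians are 0.92/0.78/0.50 and P(toxicity ≤33%) is 0.02/0.11/0.40. Both probability readings select level 3; the median-toxicity reading gives dose 0.

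**6. Same data and covariance, with β1, β2 > 0.** The 2/2 case gives medians of about 0.65/0.80/0.90 and P(toxicity ≤33%) of 0.14/0.05/0.02. No level has median toxicity below 33% or P(tolerable) of at least 33%, so the result is dose 0. The highest-posterior-probability wording has no floor of its own: it would rank level 1 first and cannot return dose 0 without a threshold. The literal reading in step 3 would also keep level 1 (1 − 0.65 = 0.35). So the constraint removes level 3 under every wording, but reaching dose 0 also depends on settling the rule.

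Plain truncation has a side effect. After a clean group 1 and before any IV patient, median toxicity at group 2 level 3 becomes 0.56, against 0.22 without the constraint.

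**The case against.** **Other sections stand in the way of the step.** Intervention makes a dose increase conditional on no dose-limiting events. The Discussion says that the first three patients in both groups receive a low dose, which conflicts with level 3 for the third intravenous patient. Trial schedule and duration requires investigator and sponsor agreement before the second and third subject of a level, and DSMB consent after a completed level. A reader might infer from the model output that a patient would in fact be given level 3; the documents do not support that, since these checks could block it. What stands against the objection is that none of them changes the posterior, and the model remains the stated basis for allocation and for the MTD.

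**Not every conceivable rule fails.** Read as a posterior mean, toxicity at level 3 after 2/2 is about 0.34 (0.338 by grid), just above 0.33, and the trial would stop. That reading is possible, but the article does not print it.

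**The model is not reassured by DLEs.** One might say that it escalates because of toxicity. It does not: median toxicity at level 3 is 0.22 before any intravenous patient and 0.21 after two DLEs. The fault is failure to learn about level 3. The first DLE matters because it hands control from the three-at-one scheme to a model that already accepts level 3.

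**Group 1 is less clear.** One might infer that dose 0 can never be reached. Under the median-toxicity reading it is reached in group 1 after 2/2. Figure 2 is not shown and covers group 1 only, so it cannot settle the group 2 path.

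**The article is condensed.** That does not help here, because model, prior matrix and rules are all printed; the point concerns what is stated.

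**Conclusion.** The point holds for the model as printed. The prior treats falling and rising toxicity as equally likely and makes levels 1 and 3 independent. After a clean group 1, 2/2 DLEs at intravenous level 1 lead every printed rule to level 3. The probability of arriving there depends on the wording: 27%/70% or about 12%/45% at true DLE rates of 10%/33%.

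This rests on three assumptions: no unprinted sign constraint, nine DLE-free patients in group 1 (three per level), and model output taken before human review. It does not show that the trial procedure as a whole would expose a patient to level 3, nor that any MTD from it would be uninterpretable. It does show that the model behind a primary objective can favour the top level after toxicity at the bottom one. That should be corrected before use.

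**What to change.** 1. Constrain both slopes to be positive, by truncating β1 and β2 at 0 or by log-normal slopes, so that p_i1 ≤ p_i2 ≤ p_i3 always holds.
2. Recalibrate the prior means and variances under that constraint. Truncating the present prior without doing so makes it much more pessimistic about level 3 (step 6 of the working).
3. Regenerate the decision trees for both groups, including group 2 after different group 1 outcomes.
4. State one allocation rule, including the condition that produces dose 0, in place of the three wordings in Analysis variables, Statistical methods and Dose escalation scheme. Reconcile it with Intervention, Trial schedule and duration, and the Discussion. Which clinical rule governs is for the sponsor and investigators to settle.

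The cost is a short change to the model specification, a prior calibration, a rerun of the decision trees and an edit of the text. No extra patients or data are needed.
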